### 2.1. Design and Setting

The BOOST DRG study is divided into two phases.

Phase A (Pilot study) is a randomized, double-blinded, crossover, six-arm study evaluating the feasibility and comparing the efficacy of three stimulation modalities: SCS, DRGS and DUAL (SCS+DRGS) on 12 patients during 3-month follow-up, which will be conducted only in Poitiers University Hospital (France). According to the phase A results, in terms of feasibility and safety, a second phase is planned, following the same design and including a larger sample of patients, internationally, to take into account the variability of practices.

Phase B (Main study) is a prospective, multicentric, randomized, double-blinded, crossover, six-arm study comparing the efficacy of three stimulation modalities: SCS, DRGS and DUAL stimulation (SCS+DRGS) on 54 patients, conducted in the Poitiers University Hospital (France), the Colmar Louis Pasteur Hospital (France) and in Genève Tower Hospital Pain Clinic/Lausanne University Hospital (Switzerland).

Phase A and phase B have the same design. Patients will be implanted with the Octrode^TM^ contact percutaneous lead for SCS and one or several Quattrode^TM^ lead(s) for the DRGS, enabling use of the three different stimulation modalities in the same patient. The leads will be connected to a single external pulse generator. Patients will be randomized in 6 different arms in a 1:1:1:1:1:1 ratio: SCS alone, DRGS alone and DUAL stimulation. During the 3-month crossover period, patients will be under the tonic conventional stimulation (TCS) waveform, whatever the stimulation modality. Each stimulation modality will be administered for 1 month. Patients will be assessed at the end of each stimulation modality period, corresponding to the 1-month, 2-month and 3-month follow-up visits. At the end of the crossover period, stimulation modality will not be changed and will be switched to the burst waveform for 1 month. Patients will be assessed at the end of this 1-month period, corresponding to the study’s 4-month follow-up visit. Patients will then decide which stimulation modality and waveform they prefer and will be assessed at 6 months and 12 months.

Patient flow and the study design are presented in Table 1 and Figure 1, respectively.

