Potential lead migration should be documented by imaging in case the patient experiences inadequate pain relief and/or for coverage after initial positive outcome. In case of lead displacement, documented by X-ray, a revision surgery will be recommended to check hardware dysfunction, including lead migration or fracture. This complication will be reported as an adverse event. Pain rating and outcomes will be analyzed taking the adverse event into account.

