### 2.5. Clinical Assessments

Randomization is carried out at the IPG implantation visit. Subjects are assessed prior to randomization, during the inclusion visit and the lead implantation visit, and at 1-month, 2-month, 3-month, 4-month, 6-month and 12-month follow-up visits. Assessments are performed by appropriately trained and delegated study staff independently from industry. Details about which information will be collected at each visit can be found in Table 1.

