#### 2.5.2. Secondary Outcomes

Secondary outcomes that will be compared between treatments and waveforms are changed between baseline and each follow-up visit in each of the following scores: pain intensity (VAS), pain surface (in cm^2^), percentage of pain covered with paresthesia and lead selectivity (percentage of paresthesia covering pain); paresthesia discomfort measured by an 11-point numeric rating scale (NRS) while sitting, standing and lying down; health-related quality of life measured by the EuroQol 5 Dimensions 5 Level (EQ-5D-5L) questionnaire; functional disability measured by the Oswestry Disability Index (ODI); anxiety and depression symptoms measured by the Hospital Anxiety and Depression Scale (HADS) and the Pain Catastrophizing Scale (PCS); and patient satisfaction measured by the Patient Global Impression of Change Scale (PGIC). Safety will be evaluated by adverse events (AE), serious adverse events (SAE) and device deficiencies from inclusion to 12-month follow-up.

Only for patients enrolled at Poitiers University Hospital: the effects of stimulation modalities on brain imaging will be measured by MRI Blood Oxygen Level-Dependent (BOLD) signal and Fractional Anisotropy (FA) resting state condition (stimulation switch off). Effects of stimulation on brain electrical activity will be measured by EEG signal of the posterior cingulate cortex (PCC), the pregenual anterior cingulate cortex (pgACC) and ventromedial prefrontal cortex (vmPFC), pgACC/vmPFC with stimulation switched on.

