Two interim analyses are planned. The first interim analysis will be conducted on data from the first 12 patients included (after the “Tonic” crossover period). In this first interim analysis, we will analyze only the safety criteria, the objective being to assess study feasibility. The second interim analysis will be conducted on data from the first 33 patients included (after the “Tonic” crossover period) and will be exclusively descriptive. No hypothesis testing will be conducted. This analysis will be conducted on primary and secondary outcomes. As the study is of long duration (3.5 years), we decided to include a second interim analysis to communicate the results to the scientific community by clearly indicating that this is an interim analysis and that the final analysis will be conducted on the total sample of 66 patients. This may lead to other projects and accelerate the progress of research on the stimulation of several anatomical targets. These results will have no impact on study completion. The final analysis on 66 patients will be considered for the report and the publications.

Only data from the crossover period will be used in the interim analysis. The statistical methods used in this interim analysis will be similar to the methods used in final analysis described above. No adjustment of the final analysis *p*-values will be conducted as the interim analysis results do not influence in any way the course or the conduct of the study.

A significance level of 0.05 will be considered in this study (after taking into account multiple testing corrections) and all tests will be two-sided.

All the analyses will be conducted based on an Intention-To-Treat (ITT) principle using complete cases. No missing data imputation will be conducted. An initial safety analysis will be conducted on the first 12 patients to assess the initial safety of implementing patients with both DRG and SCS stimulations. A final safety analysis will be conducted on the 66 patients. Frequencies of adverse events and deviations from protocol will be compared between the treatments following an ITT analysis.

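### The adverse-event comparison between modalities is valid for stimulation-related harms but cannot estimate the harm of carrying a DRG lead or an SCS lead; hardware and procedure events need their own analysis

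*Protocol article*

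**What the plan says.** All references are to the protocol article.

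- **Analysis.** Section 2.7.2: "Frequencies of adverse events and deviations from protocol will be compared between the treatments following an ITT analysis". The same section plans an initial safety analysis of the combined implant in the first 12 patients and a final one in 66.
- **Hardware.** Section 2.1 gives each patient one SCS lead and "one or several Quattrode^TM^ lead(s) for the DRGS", "enabling use of the three different stimulation modalities in the same patient".
- **Exposure.** Section 2.1: "Each stimulation modality will be administered for 1 month". After month 4 the patient chooses modality and waveform.
- **Randomisation.** Section 2.5: "Randomization is carried out at the IPG implantation visit". This follows lead implantation and the 7-day trial (section 2.3.2).
- **Collection.** Section 2.5.2: "Safety will be evaluated by adverse events (AE), serious adverse events (SAE) and device deficiencies from inclusion to 12-month follow-up".
- **Lead displacement.** Section 2.3.1: "This complication will be reported as an adverse event". Imaging for migration is prompted by inadequate relief or coverage after a good start.

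**The concern.** The randomised factor is which lead is switched on, not which lead is in the body. An infection, fracture or migration of a DRG lead can occur in any of the three months, including an SCS-alone month. Counted by allocated modality, such an event may fall under a modality that did not cause it.

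The sentence also sets no time window. Safety data run from inclusion to month 12, but modality is randomised within patient only from M0 to M3. Lead-implantation and lead-trial events precede any allocation. Events after M4 occur under a modality the patient picked, usually because it worked for them.

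The article itself gives reasons to expect lead-specific problems: foraminal fibrosis and spinal instrumentation as obstacles to DRG placement (section 3.3), and particular care over DRG anchoring (section 2.3.1). If the modality comparison shows no difference, it could be read as evidence that the DRG lead adds no hardware risk. The comparison cannot support that.

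**Working it through.** **What the article gives.** It states no adverse-event rate, precision or power for safety, so there is no figure to reproduce. The planned 48 evaluable patients (66 in total) were set for the efficacy endpoint and do not bear on this point. N = 66, three 1-month periods and the two-sided 0.05 level come from the article. The lead event rates and the detection fraction below are assumptions.

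**Time windows after M0.** Of 12 months, 3 are the randomised crossover, 1 is the burst month on the last allocated modality, and 12 − 4 = 8 are on the patient's choice.

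**Attribution.** The article gives no rule. The working charges an event to the modality allocated when it is detected, which is the natural reading of a comparison between treatments in a crossover.

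**Model.** Let s and d be the 3-month probabilities of an SCS-lead and a DRG-lead event, with timing uniform over the three months. Let f be the chance that a fault in an inactive lead is detected, relative to an active one. Undetected faults are not carried into a later month. Ignoring the small overlap of two events in one month, the expected counts are:

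- SCS month: N(s + f·d)/3
- DRGS month: N(d + f·s)/3
- DUAL month: N(s + d)/3
- DRGS-to-SCS ratio: (d + f·s)/(s + f·d)

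**Numbers for s = 5%, d = 15% (true ratio 3.0).**

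- f = 1: each modality 66 × 0.20/3 = 4.4; ratio 1.0.
- f = 0.5: SCS 66 × 0.125/3 = 2.75; DRGS 66 × 0.175/3 = 3.85; DUAL 4.4; ratio 1.4.
- f = 0: SCS 66 × 0.05/3 = 1.1; DRGS 66 × 0.15/3 = 3.3; DUAL 4.4; ratio 3.0.

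Simulation (10,000 trials, overlap counted once) gave 4.36/4.36/4.36, 2.70/3.82/4.31 and 1.10/3.30/4.33. Cochran's Q across the modalities rejected in 5%, 7% and 18% of trials. The first equals the significance level.

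**Tabulated by lead.** SCS 66 × 0.05 = 3.3; DRG 66 × 0.15 = 9.9. Exact McNemar power was 37%.

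| Assumed rates, SCS / DRG lead | By modality, rejection f = 1 to f = 0 | By lead, expected events | By lead, power |
|---|---|---|---|
| 5% / 10% | 5% to 11% | 3.3 vs 6.6 | 11% |
| 5% / 15% | 5% to 18% | 3.3 vs 9.9 | 37% |
| 5% / 20% | 5% to 28% | 3.3 vs 13.2 | 68% |

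**Precision of the by-lead estimate.** For 5% and 15%, with the two leads failing independently, the expected discordant counts are b = 66 × 0.15 × 0.95 = 9.405 and c = 66 × 0.05 × 0.85 = 2.805. The paired difference is (9.405 − 2.805)/66 = 10 percentage points. Its standard error is √(12.21 − 6.6²/66)/66 = √11.55/66 = 0.0515, so the 95% interval is about ±10 points. The right quantity can be estimated, but not precisely.

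**The case against.** The strongest reply is that the sentence does what it should. The treatments are stimulation modalities, these are what is randomised, and comparing events by allocated modality is the proper contrast for stimulation-related harm. The stated objectives do not ask whether one lead type is more harmful than the other. This stands, and the comparison should be kept for that purpose.

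A reader might go further and infer that a DRG-lead excess would be hidden by the trial, with all lead and procedure harms spread evenly over the modalities. The documents do not support that:

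- Harms of lead implantation and of the lead trial come before randomisation. They belong to no modality and are not spread over three.
- Even spreading needs f = 1. Because section 2.3.1 ties migration imaging to loss of relief or coverage, detection probably depends partly on the active lead, and part of an excess would then reappear under DRGS and DUAL.
- Displacement is confirmed by X-ray and reported as an adverse event, device deficiencies are collected, and whole-cohort safety analyses are planned. Nothing rules out a table by lead.

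It is also fair that attribution rules and form fields often sit in a full protocol or SAP, which is not shown, and that the article nowhere claims equal hardware safety. A by-lead significance test would be weak and would set one SCS lead against one or several DRG leads.

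What remains is that the article does fix one comparative safety analysis, without limiting it by event type or time window. Later detail that follows the sentence as written would inherit the mixture.

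**Conclusion.** The point holds in this limited form. As written, the comparison pools stimulation-related events, which it can attribute, with hardware events, which it cannot, and with events that have no randomised modality. For hardware events after M0, the dilution is complete if faults are found whichever lead is active and partial if they are found through loss of relief. At assumed rates of 5% and 15%, the DRGS-to-SCS ratio shown lies between 1.0 and 3.0 against a true 3.0, and the chance of a significant modality difference between 5% and 18%. These sizes rest wholly on assumed rates, uniform timing and the assumed detection fraction. The structural conclusion, that the harm of having either lead is not estimable from this contrast, rests only on every patient carrying both kinds of lead.

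The change is worth making because it is cheap and affects what the trial can conclude on safety. It does not call the design or the data collection into question.

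**What to change.** Replace the sentence in section 2.7.2 with three parts:

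- **(a) Stimulation-related events**, compared by allocated modality within patient over M0–M3. Tabulate the M3–M4 burst month separately by last allocated modality; the waveform differs there, and section 3.4 raises its own concern about DRG overstimulation.
- **(b) Procedure, lead and device events**, from lead implantation onward in all implanted patients, including lead-trial failures. Tabulate by component (SCS lead, DRG lead, generator or pocket, surgery), per patient and per lead because the number of DRG leads varies. Give estimates with confidence intervals and make no modality comparison.
- **(c) Events after M4**, described by chosen modality and labelled non-randomised.

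Add a statement that a null result in (a) does not show equal hardware safety.

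Cost: revised wording and one component field on the adverse-event form. Each table will hold fewer events. Recruitment, randomisation and visits are unchanged.

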#### 2.7.3. Extraction of Predictors of Long-Term Stimulation Efficacy

Long-term stimulation efficacy will be defined as being a “good responder”, according to the composite factor described in the Section 2.5.2 at 12-month follow-up.

The link between stimulation efficacy and each clinical, sociodemographic and psychological factor at baseline will be tested in a bivariate analysis. The link between quantitative variables and the long-term efficacy will be analyzed using *t*-tests or Wilcoxon test. The link between nominal qualitative variables and the long-term outcome will be tested using a Chi-squared test or an exact Fisher test depending on the number of patients per modalities. The link between ordinal variables and the long-term outcome will be tested using Cochran–Armitage test. Variables that are significant at a 5% level will be included in a multivariate logistic regression model where we will adjust for the type of stimulation and waveform by including interaction terms between the factors and the type of therapy.

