### Aims and Objectives

The BOOST DRG study is a randomized, controlled trial comparing the efficacy of SCS vs. DRGS vs. combination of SCS+DRGS (DUAL) and TCS vs. burst in a crossover design in patients with chronic lower limb neuropathic pain and/or neuropathic back pain.

The primary objective of this study is to compare the efficacy of SCS vs. DRGS vs. DUAL on global pain relief in patients with chronic lower limb neuropathic pain and/or neuropathic back pain.

Secondary objectives are to compare pain intensity, pain surface and paresthesia coverage surface to assess positional or postural effects on paresthesia, to compare changes in quality of life, functional disability and psychological state, to assess patient satisfaction and, finally, to compare the effects of stimulation modalities on brain imaging based on fMRI and EEG. Using this study data, we will extract baseline factors associated with long-term stimulation efficacy. These predictors will be included in a predictive model.

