We will also evaluate stimulation efficacy using a published and clinically validated composite factor that allows for the multidimensional evaluation of patients [59]. Patients having at least three of the criteria listed below will be considered as good responders:Regaining functional capacity: having at least a 30% decrease in Oswestry Disability Index (ODI) percentage.Adequate global pain relief: having at least a 50% decrease in the Visual Analogic Scale (VAS).Improvement in quality of life: having at least a 0.2 increase in the EuroQol-5 Dimensions (EQ-5D) questionnaire.Decrease in psychological distress: having a decrease of at least 1.4 points in the Hospital Anxiety and Depression Scale (HADS) depression score.Decrease of at least 30% in pain surface (percentage of cm^2^): pain surface and its properties will be assessed using a pain mapping tool.Having a Patient Global Impression of Change (PGIC) score of at least 6/7.Drug intake: drug intake will be measured using the Medication Quantification Scale (MQS) and a reduction of at least 3.4 points will be considered as meaningful.

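### Baseline HADS depression, EQ-5D and MQS are screened against a composite built partly from absolute changes in those same scores, so a worse baseline can look like a predictor of efficacy

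*Protocol article*

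**What the plan says.** The objective is in the Aims and Objectives section: "Using this study data, we will extract baseline factors associated with long-term stimulation efficacy". The sentence after it says that these factors will enter a predictive model.

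Section 2.7.3 fixes the analysis. The outcome is good response "according to the composite factor described in the Section 2.5.2 at 12-month follow-up". The candidate set is stated generally: "The link between stimulation efficacy and each clinical, sociodemographic and psychological factor at baseline will be tested in a bivariate analysis". Quantitative factors are tested by t-test or Wilcoxon test. Those significant at 5% enter one multivariate logistic model, with interactions between the factors and the type of therapy.

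Section 2.5.2 defines the outcome: "Patients having at least three of the criteria listed below will be considered as good responders". There are seven criteria:
- Three are absolute changes: "having a decrease of at least 1.4 points in the Hospital Anxiety and Depression Scale (HADS) depression score", "having at least a 0.2 increase in the EuroQol-5 Dimensions (EQ-5D) questionnaire", and, for drug intake on the MQS, "a reduction of at least 3.4 points will be considered as meaningful".
- Three are percentage changes: "having at least a 30% decrease in Oswestry Disability Index (ODI) percentage", a 50% fall in VAS and a 30% fall in pain surface.
- One, PGIC of at least 6/7, is not a difference from a baseline score.

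Table 1 schedules HADS, EQ-5D-5L and ODI at the inclusion visit. Section 2.5.3 lists analgesic treatments among the data collected at screening and baseline. Nothing in Section 2.7.3 sets the component scores apart from other candidates.

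**The concern.** Outcome and candidate share a measurement. When success is a fall of a fixed number of points, the starting score affects success in two ways that have nothing to do with stimulation.

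The first is room to move. A patient who starts at HADS depression 0 or 1, EQ-5D above 0.8 or MQS below 3.4 cannot meet that criterion at all. The second is regression to the mean. A baseline that is high partly through measurement error tends to be followed by a lower score, and the criterion is met without benefit.

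The interactions with type of therapy do not remove either route, and more patients would not help: a coupling of this kind becomes more significant as the sample grows. It is therefore a different matter from overfitting by p-value screening. At stake is the reading of a stated secondary objective. Worse depression, worse quality of life or heavier drug intake could be reported as marking patients in whom stimulation works.

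**Working it through.** **Inputs from the article.** The seven criteria and the three-of-seven rule (Section 2.5.2); two-sided tests at 5% per factor (Sections 2.7.2 and 2.7.3); 66 patients and 17% dropout (Section 2.7.1), so 66 × 0.83 = 54.8, about 55 evaluable. The predictor analysis has no power or error-rate figure of its own to reproduce.

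**Assumptions (not in the article).** Baseline mean (SD): HADS depression 8–8.5 (4), EQ-5D 0.40–0.45 (0.22–0.25), MQS 12–14 (8–9), ODI 48 (14), VAS 7.3 (1.3), pain surface 300 (150). Reliability 0.6–0.95, shared severity 0–0.6, mean benefit 0–45%.

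**Step 1: room to move.** With normal baselines at 8.5 (4), 0.40 (0.25) and 14 (9), the share unable to meet the criterion is:
- HADS depression: Φ((1.4 − 8.5)/4) = Φ(−1.78), about 4%.
- EQ-5D: 1 − Φ((0.8 − 0.40)/0.25) = 1 − Φ(1.60), about 5%.
- MQS: Φ((3.4 − 14)/9) = Φ(−1.18), about 12%.

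**Step 2: regression to the mean.** Write the observed baseline as X = T + e, with variance σ² and reliability ρ, for a score where high is bad.
- Constant-shift benefit b: Y = T − b + e′, so X − Y = b + e − e′ and Cov(X, X − Y) = (1 − ρ)σ². If b is the same for all, the correlation is √((1 − ρ)/2): √0.20 = 0.45 at ρ = 0.6, √0.125 = 0.35 at ρ = 0.75, √0.025 = 0.16 at ρ = 0.95. Variation in b lowers these.
- Proportional benefit with mean p: the covariance becomes pρσ² + (1 − ρ)σ². At p = 0.3 and ρ = 0.75 this is (0.225 + 0.25)σ² = 0.475σ², against 0.25σ² under constant shift.
- A percentage cut-off c under constant shift is met when b − cT + (1 − c)e − e′ ≥ 0. The covariance of this margin with X is (1 − c)(1 − ρ)σ² − cρσ². At ρ = 0.75 that is (0.175 − 0.225)σ² = −0.05σ² for c = 0.3, and (0.125 − 0.375)σ² = −0.25σ² for c = 0.5. These criteria pull weakly or the other way.

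**Step 3: the planned test.** Simulated trials (1,500 or 6,000 per setting; n = 48, 55 and 66), with benefit drawn independently of baseline and t-tests at 5%. At 1,500 trials the standard error at a rate of 5% is √(0.05 × 0.95/1500) = 0.6 points, so small excesses over 5% are noise.

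| Share of trials significant | HADS depression | EQ-5D | MQS |
|---|---|---|---|
| Against its own criterion alone | 27–90% | 24–93% | 56–98% |
| Same, reliability 0.95 | 13% | 14% | 38% |
| Against composite, proportional | 9–14% | 7–13% | 9–15% |
| Against composite, constant shift | 5–9% | 5–10% | 5–10% |

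One constant-shift setting shows the dilution (n = 55, reliability 0.75, shared severity 0.3, responder rate 64%). Against their own criteria the three scores are significant in 49%, 47% and 78% of trials. Against the composite the figures are 6.0%, 5.4% and 6.2%.

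At least one of the three scores is falsely significant in 22–31% of trials (proportional) or 13–20% (constant shift). Three independent 5% tests would give 1 − 0.95³ = 14%.

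**Step 4: direction.** Under proportional benefit 85–99% of the false signals point to a worse baseline. Under constant shift it is mostly 50–90%, falling to 33–44% at reliability 0.95.

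**Step 5: removing the score's own criterion.** Testing each score against at least three of the other six gives about 4–7% when errors are independent. PGIC of at least 6/7 alone gives about 5%. If baseline errors correlate across questionnaires and benefit is proportional, the full composite gives 13–23% for the three scores, and leaving out the own criterion still gives about 8–14%.

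**Step 6: sample size.** At n = 200 (reliability 0.7, no shared severity) the full composite gives 23–29% (proportional) or 14–21% (constant shift). Without the own criterion it gives 4–6%.

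**The case against.** The strongest reply is that Section 2.7.3 is headed as an extraction of predictors, and the objective ends in a predictive model. For forecasting this composite, baseline severity is legitimate information, including the fact that a patient near the floor cannot meet a criterion. Under proportional benefit, patients with a worse baseline really do gain more points and really do meet the composite more often, so the association is true of the outcome as defined. This stands, and it is why the full-composite model should stay. It does not cover the other half of the objective, finding factors associated with stimulation efficacy: the planned test cannot tell a patient who responds better from one whose starting score makes the cut-off easier to reach.

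A reader might infer that the plan will produce artefact predictors, or that its results would misdirect patient selection. The documents do not support that. Three of seven criteria are affected, the rule needs any three, the percentage criteria can pull the other way, and under constant shift the inflation can be close to nil. For any one score, most trials would show no false signal. The article draws no selection rule from this analysis.

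It is also true that no candidate list is given and that a full analysis plan may supply one. But the article itself fixes the outcome, the test and a candidate set covering each clinical and psychological factor, and HADS is one of the few psychological instruments scheduled. Finally, recomputing the outcome candidate by candidate cannot replace the planned analysis, because one multivariate model needs one outcome. That also stands, and it limits the remedy to a check.

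**Conclusion.** The point holds as a moderate bias in how a secondary, exploratory analysis would be read. For baseline HADS depression, EQ-5D and MQS the coupling with the outcome is arithmetic and the article states no safeguard. The false-positive rate per score is about 7–15% if benefit is proportional and about 5–10% if it is a constant shift, against a nominal 5%. It is higher if baseline errors correlate across questionnaires. ODI, VAS and pain surface are little affected unless errors correlate. All these sizes rest on assumed means, SDs, reliabilities and correlations. Only the existence of the coupling, not its size, follows from the article alone. The primary comparison of SCS, DRGS and DUAL is not touched.

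**What to change.** Keep the screen and the single multivariate model on the full composite, described as prediction of that composite. Add to Section 2.7.3 a prespecified check for baseline HADS depression, EQ-5D and MQS, optionally also for ODI, VAS and pain surface:
- Test each score against good response recomputed without its own criterion (at least three of the other six).
- As a second check, test it against PGIC of at least 6/7.
- Interpret the score as a factor associated with stimulation efficacy only if the association persists there. Otherwise report it as baseline-dependent.

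The cost is a few derived variables and a sentence or two of text, with no new data. The reduced composite is slightly harder to meet, so a little power is lost for these scores. The check weakens the coupling but does not fully remove it when baseline errors are correlated, and the report should say so.

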To address these challenges, we designed a randomized controlled trial (RCT) with a 3-month crossover design, where SCS, DRGS or SCS+DRGS (DUAL) will be proposed to a single patient presenting with refractory chronic lower limb neuropathic pain (e.g., CRPS, diabetic foot peripheral neuropathy, foot and ankle peripheral neuropathy, radicular pain associated with PSPS-T2) and/or documented neuropathic refractory back pain. After the crossover period, all patients will be switched to burst waveform with 1-month follow-up, and at 4-month follow-up, they will be asked to choose SCS, DRGS or SCS+DRGS with tonic conventional or burst waveform.

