### 2.7. Statistical Analysis

#### 2.7.1. Sample Size and Power Calculations

In the ACCURATE study [24], the authors reported a significant difference between DRGS and conventional SCS for the treatment of the CRPS and causalgia using the following primary end point: “VAS decrease percentage ≥ 50% during lead trial and at 3-month follow-up and no incidence of neurological deficits due to stimulation”. They found that 81.2% of patients (56/69) responded to DRGS vs. 55.7% of patients (39/70) to SCS at 3-month follow-up. These data allowed us to estimate the necessary sample size that suffices to demonstrate a significant difference between the DRGS and conventional SCS. No data are available in the literature concerning DUAL stimulation. We estimate that DUAL stimulation superiority might arise from combining the effects of and mechanisms of action of both stimulation modalities.

With a level of significance at 0.05 and a power of 90%, we found that a number of patients set at 48 should be adequate to demonstrate a significant difference between the success proportions in SCS, DRG and DUAL stimulations in a six-arm crossover design.

Considering the possibility of a potential dropout (17%—lost to follow-up and possible explanted patients, which is the drop-out rate we observed in our previous studies [4,5]), and in order to have a sufficient number of patients allowing us to address secondary objectives, a total of 66 patients are planned to be included in the study.

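### The 12-month predictor model selects factors by a 5% univariable screen and adds therapy interactions in about 55 patients, so a retained noise factor would look predictive

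*Protocol article*

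**What the plan says.** The aims in the protocol article include extracting baseline factors associated with long-term efficacy, and add that "These predictors will be included in a predictive model". Section 2.7.3 gives the method. The outcome is being a good responder at 12 months on the composite of Section 2.5.2. The link with "each clinical, sociodemographic and psychological factor at baseline will be tested in a bivariate analysis". After that, "Variables that are significant at a 5% level will be included in a multivariate logistic regression model", and the model adjusts for stimulation type and waveform "by including interaction terms between the factors and the type of therapy".

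Three other statements set the scale:

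- **Sample:** Section 2.7.1 says that "a total of 66 patients are planned to be included in the study" and allows for "potential dropout (17%—lost to follow-up and possible explanted patients".
- **Missing data:** Section 2.7.2 analyses complete cases and says "No missing data imputation will be conducted".
- **Therapy after month 4:** the Introduction says of patients that "they will be asked to choose SCS, DRGS or SCS+DRGS with tonic conventional or burst waveform". There are therefore up to six therapy combinations, chosen by the patients themselves.

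Section 2.7.2 also sets a study-wide two-sided level of 0.05 that applies after multiple testing corrections. The only correction it names is Holm–Bonferroni, for pairwise comparisons.

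**The concern.** The same patients are used to choose the factors and to estimate their effects. A factor that passes a 5% screen by chance enters the model with an effect already inflated by the selection. Each retained factor then brings several interaction terms, fitted in a sample whose smaller outcome class may be only about 22 patients. Both steps raise the apparent fit without raising true predictive ability.

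This is a rule that the article fixes, so the objection is not about missing detail. If it is followed as written, a secondary objective could end in a model that discriminates well in the trial's own patients and not at all in new ones.

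**Working it through.** The article gives no sample size, candidate count or expected performance for this model, so there is no stated figure to reproduce. Section 2.7.1 sizes the trial for the primary comparison (48 patients). 48 / (1 − 0.17) = 57.8, or 58, and the article attributes the rest of the 66 partly to secondary objectives.

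**1. Patients available.** 66 × 0.83 = 54.8, about 55 complete cases at month 12.

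**2. Smaller outcome class.** The responder rate is not stated. At an assumed 60%, 55 × 0.40 = 22. At 50% to 80% it is about 28 down to 11.

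**3. Coefficients for one retained continuous factor** (factor + therapy + interactions, intercept not counted). The article does not settle how therapy is coded.

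| Therapy coding | Coefficients | Smaller-class patients per coefficient (22) |
|---|---|---|
| 3 levels | 1 + 2 + 2 = 5 | 4.4 |
| Modality + waveform, additive | 1 + 3 + 3 = 7 | 3.1 |
| Six crossed cells | 1 + 5 + 5 = 11 | 2.0 |

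**4. Chance that the screen retains a noise factor.** The number of candidates K is not stated. Sections 2.5.1 to 2.5.3 and Table 1 name roughly 20 baseline items, so K = 15 to 25 is assumed. For independent candidates the chance is 1 − 0.95^K:

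- K = 15: 54%
- K = 20: 64%
- K = 25: 72%

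With pairwise correlation 0.3, simulation gives about 46–47%, 54–55% and 61–62%. Allowing for variation between simulation runs, the range is about 43–73%.

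**5. What the model then looks like.** Null data were simulated with n = 55, 60% responders, continuous candidates and equally likely therapy levels. Candidates were screened by t-test at 5%, and a logistic model was fitted with therapy, the retained factors and their interactions. The article plans no AUC; it is used here only to measure how good the model would appear. Where at least one factor was retained:

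| Therapy coding | Mean apparent AUC | AUC in new patients | Fits with diverging coefficients |
|---|---|---|---|
| 3 levels, or modality + waveform | 0.76–0.81 | 0.50 | about 4–13% |
| Six crossed cells | 0.84–0.86 | 0.50 | about 62–72% |

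The divergence figures depend on the criterion. Counting any coefficient above 10 in absolute value gives 6–13% and 74–82%. Over a wider grid (10 to 30 candidates, 50–80% responders), the overall likelihood-ratio test of the retained model has p < 0.05 in 39–65% of those runs, where 5% would be nominal.

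**6. Counting all noise trials at 60% responders,** including those that retain nothing, an apparent AUC of 0.8 or more occurs in 11–27% (3-level coding) or 30–53% (six cells).

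**7. If the screen were corrected.** Bonferroni over 20 independent candidates gives 1 − (1 − 0.05/20)^20 = 4.9%, against 64% uncorrected.

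**The case against.** The strongest reply is that the figures rest on inputs the article does not give, and that the worst of them need the largest therapy coding. That stands. Eleven coefficients and frequent divergence belong to six fully crossed cells. Under the smaller codings most fits are estimable, so a reader who inferred that the model is generally non-estimable would go beyond the text. The inflated apparent AUC, however, appears under all three codings.

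A reader might also infer that the plan is bound to report a strong model from noise. It is not: about 27–57% of noise trials retain nothing. With 15 correlated candidates the chance of retaining a factor is below one half.

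The study-wide sentence in Section 2.7.2 could be read as covering the screen, which would cut false selection to about 5%. Section 2.7.3 does not read that way, and no correction is named for it. A correction would also leave the interaction overfitting in place whenever a factor does pass.

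Two further inferences are not supported. The article does not say that the model will be used to select patients for treatment; it speaks only of a predictive model. And its silence on penalisation, validation and calibration is no defect in itself, since a fuller protocol or analysis plan may cover them. What such a document could not do is keep this entry rule and these interactions and avoid the problem.

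Finally, whether factor effects depend on therapy is a legitimate question, and Section 3.1 shows interest in it. That argues for showing interactions as exploratory. It does not make them estimable with any precision in 55 patients.

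**Conclusion.** The point holds as a defect in a stated analysis rule for a secondary objective. With about 55 complete cases, 15 to 25 candidates (correlation 0 to 0.3) and 60% responders, the written procedure retains at least one noise factor in about 43–73% of trials. With about 20 or more candidates that is more likely than not. The retained model then appears to discriminate at a mean AUC of 0.76–0.86, depending on therapy coding, when the truth is 0.50. The candidate count, responder rate, correlation and coding are assumptions, because the article states none of them. Sections 2.7.2 and 2.7.3 also need reconciling on whether the 5% screen is corrected for multiplicity. The primary crossover comparison is untouched.

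**What to change.** - Replace the 5% univariable screen as the entry rule with a short candidate list, chosen in advance on clinical grounds and entered together in a penalised (ridge or Firth) logistic model.
- Code therapy with the fewest terms that serve the purpose. Keep factor-by-therapy interactions out of the main predictive model, or show them only as exploratory.
- Report discrimination and calibration corrected for optimism by a bootstrap that repeats every modelling step.
- Present the bivariate tests as descriptive, and state whether the multiplicity sentence in Section 2.7.2 applies to them.
- Label the model exploratory.

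This needs no new data and no design change. The cost is a little more analysis work, less favourable reported performance, and no firm claims that a factor's effect differs by therapy.
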